### Participants and recruitment procedure

The research team will formally engage with the Board of Executives of selected universities in Ho Chi Minh City, explaining the study’s objectives and extending invitations for their participation. The study will be advertised via posters, email and the fan pages of either the Department of Student Affairs or the Student Union at each enrolled university. To encourage recruitment, advertisements for STABLE will include a brief description of the incentives for participation (VND 220,000 or approximately US$9 per student per month for the duration of involvement in the study) and free spectacles for participants identified with uncorrected myopia (see below).

Prior to recruitment, potential student participants will be asked to conduct a smartphone-based vision self-assessment using WHOeyes, the WHO’s free smartphone application for vision monitoring available in Vietnamese [20, 21]. Those failing that assessment (an estimated 40% based on pilot testing who have distance visual acuity in either eye < 6/12, with normal near visual acuity in both eyes) are at increased risk of refractive error and will be invited to join the pre-evaluation phase of the study. Students providing informed consent and meeting the initial inclusion criteria below on a brief survey will have DAS devices fitted to their motorcycles. These instruments are equipped with front and rear, driver-facing video cameras and accelerometers, and can detect changes in speed and direction (such as swerving).Enrolled in one of the selected faculties of a participating universityAged 18 to 23 yearsSole driver of their motorcycleUse their motorcycle as their primary means of transportDrive ≥ 25 km/week by self-reportHold a valid driving licence if required (for motorcycles having an engine capacity > 50 cc)Failed the WHOeyes vision self-assessment in at least one eye

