### Study intervention

Over the 72 weeks of the study, an estimated 250 students from the 25 clusters, randomised in groups of five clusters, will enter the intervention condition. Each of these participants will receive a free pair of spectacles with spherocylindrical power in each eye as measured during refraction by an optometrist. Refractive power will be based on non-cycloplegic automated refraction (QuickSee, Plenoptika, Cambridge, USA) and subjective refinement. Spectacle-wear compliance will be assessed and recorded throughout the trial based on footage from the driver-facing cameras. Replacement spectacles will be provided free of charge as needed due to loss or breakage. Research staff will communicate with trial participants observed having poor compliance in order to improve their use of the spectacles. Myopia progression in this age group is not expected to be clinically meaningful over the 72 weeks, so there are no provisions for routine re-evaluation of refractive power. However, participants complaining of declining vision or symptoms associated with spectacle wear will be examined at study clinics, with replacement spectacles provided as needed.

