### Sample size

Unpublished data from Dynamic Vision, an organisation currently collecting CNC events from motorcycle drivers in Vietnam, were used to inform the power calculation. Results showed an estimated mean event rate of 1.67 CNC events per 1000 km driven (standard deviation [SD] = 0.556). For a postulated, clinically meaningful 10% reduction in CNC events, a stepped-wedge cohort design comprising six sequences of seven myopic participants per cluster (a 28% prevalence, below the 40% figure observed during pilot testing with the WHOeyes app), a coefficient of variation of cluster sizes of 3, and five clusters per sequence with Individual Auto Correlation (IAC) of zero, confer 90% power (mean difference = 0.167, SD = 0.556; intraclass correlation [ICC] = 0.02 [0.01–0.05]) [23]. This would be achieved by collecting DAS data from 175 students over the course of 72 weeks. To achieve this, 5200 students will be invited to self-assess their vision using WHOeyes. Pilot data indicate that approximately 12%, or 625 students, will fail that assessment and be eligible to join the preliminary phase of the study, with placement of DAS units on their motorcycles. An estimated 250 (40% of those failing the WHOeyes self-assessment) will have eligible, uncorrected/under-corrected myopia detected on their subsequent eye examination by an optometrist. They will then be assigned to the intervention condition and given free spectacles. With a 30% dropout rate, this will result in complete datasets for 175 participants over the course of the trial.

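### The inputs reported for the 90% power (six sequences, cluster-size CV of 3, a 28% prevalence margin) are wrong, although 90% is close to what the trial's real layout gives

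*Protocol article*

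**What the plan says.** The Sample size section describes "a stepped-wedge cohort design comprising six sequences of seven myopic participants per cluster". It calls the resulting seven per cluster "a 28% prevalence, below the 40% figure observed during pilot testing with the WHOeyes app", then adds "a coefficient of variation of cluster sizes of 3, and five clusters per sequence", with an individual autocorrelation of zero and an ICC of 0.02 (range 0.01 to 0.05). These are said to "confer 90% power (mean difference = 0.167, SD = 0.556"). The same section then says that 175 students suffice, reached as 40% of 625 = 250 eligible, less 30% dropout.

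Elsewhere the layout is different. The Abstract (Methods) has 25 clusters of 25 students, with five clusters examined every 12 weeks. The Study intervention section says that, over 72 weeks, "an estimated 250 students from the 25 clusters, randomised in groups of five clusters, will enter the intervention condition". Randomisation, allocation and concealment confirms 125 participants per step, 25 per cluster.

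The 40% also appears in Participants and recruitment procedure, for those failing the WHOeyes self-test: "an estimated 40% based on pilot testing who have distance visual acuity in either eye < 6/12". In Sample size it is the share of WHOeyes failures found to have eligible myopia, and about 12% of invitees are expected to fail and be eligible to join.

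**The concern.** Three printed inputs conflict with the trial or with each other.

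- **Layout.** The number of sequences implies five more clusters and 35 more participants than the trial will have.
- **Cluster-size CV.** A value of 3 cannot arise in clusters of the planned size, and would lower power markedly if it had been used.
- **Prevalence margin.** The 28% is presented as a cautious prevalence, which tells a funder or the DMEC that the eligible yield could fall from 40% to 28% with power intact. The arithmetic gives no such room.

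The last is the most consequential. Eligibility is known only at each cluster's eye examination, while the Trial status section says all participants must be included at the outset. A low yield would therefore emerge after recruitment had closed.

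**Working it through.** **Inputs (Sample size section).** Mean difference d = 0.167 (10% of 1.67), SD = 0.556, ICC = 0.02, individual autocorrelation 0, seven participants per cluster, five clusters per sequence. Assumed because not stated: two-sided alpha 0.05, cluster autocorrelation 1, and one observation per participant per period.

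**Formula.** Stepped-wedge linear mixed model with fixed period effects and a random cluster effect. For I clusters, T periods and m per cluster-period, let s² = SD²(1 − ICC)/m and t² = ICC × SD². Let X be the treatment indicator, U the sum of X over all cluster-periods, W the sum over periods of squared period totals of X, and V the sum over clusters of squared cluster totals of X. Then

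Var = I s²(s² + T t²) / [(IU − W)s² + (U² + ITU − TW − IV)t²], and power = Φ(d/√Var − 1.96).

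With m = 7: s² = 0.309136 × 0.98/7 = 0.04328 and t² = 0.02 × 0.309136 = 0.00618.

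**Step 1: the trial's layout.** 25/5 = 5 sequences and 72/12 = 6 periods; 25 × 7 = 175. I = 25, T = 6, U = 75, W = 1375, V = 275. Var = 0.002679, SE = 0.0518, d/SE = 3.226, power **89.7%**. This reproduces the stated 90%. Over the quoted ICC range it is 91.7% (0.01) to 86.8% (0.05).

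**Step 2: the layout as printed.** 6 × 5 = 30 clusters; 30 × 7 = 210. I = 30, T = 7, U = 105, W = 2275, V = 455. Var = 0.001889, SE = 0.0435, d/SE = 3.843, power **97.0%** with equal clusters (96.7% if six sequences are fitted into six periods).

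**Step 3: the CV of 3.** Sizes between 0 and 25 with mean 7 have variance at most 7 × (25 − 7) = 126, so the maximum CV is √126/7 = **1.60**. Binomial variation alone gives √(25 × 0.28 × 0.72)/7 = 0.32. Had 3 been used, the inflation [1 + ((CV² + 1)m − 1)ICC]/[1 + (m − 1)ICC] = (1 + 69 × 0.02)/(1 + 6 × 0.02) = 2.38/1.12 = 2.125.

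| Layout, ICC 0.02 | Equal sizes | CV 3, inflation formula | CV 3, simulated gamma sizes |
|---|---|---|---|
| Five sequences | 89.7% | 60.0% | about 65–71% |
| Six sequences | 97.0% | 75.1% | about 78–86% |

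No cell combining the printed inputs gives 90%. The nearest is 88.6%, for six sequences with CV 3 by the formula, and only at ICC 0.01. For comparison, five sequences give 89.4% at CV 0.3 and 89.1% at CV 0.43 (an SD of 3 on a mean of 7: 3/7).

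**Step 4: the 28%.** 7/25 = 0.28 = 0.40 × (1 − 0.30). The same chain in totals is 625 × 0.40 = 250 and 250 × 0.70 = 175 = 25 × 7. The 28% is thus the retained fraction at a 40% prevalence, not a lower prevalence.

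**Step 5: a true 28% yield.** 625 × 0.28 × 0.70 = 122.5, or 4.9 per cluster. s² = 0.309136 × 0.98/4.9 = 0.06183, Var = 0.003664, SE = 0.0605, d/SE = 2.759, power **78.8%** (81.1% at ICC 0.01, 75.1% at ICC 0.05).

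**Step 6: the two uses of 40%.** Of 5200 invitees, 40% is 2080 and 12% is 624. The 12% matches the planned 625; the 40% in the recruitment section describes a different quantity from the 40% in Sample size.

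**The case against.** The strongest reply is that the stated power is right for this trial. Five sequences of five clusters with seven completers give 89.7%, so the six is most likely a slip for six periods, and the 3 may be a misprint or an SD. On either reading of the CV, power stays at about 89%. This stands. A reader might infer from the printed inputs that the 90% was computed for some other design, or that the trial is underpowered because it has one sequence fewer or because its CV is 3. The documents do not support that: the 90% matches the real layout and not the six-sequence one, and a CV of 3 cannot have produced 90% at ICC 0.02.

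It can also be said that nobody plans a 28% yield together with 30% dropout, and that treating dropouts as contributing nothing is pessimistic. Dropout is applied to people who already have control-period data, 175 counts complete datasets, and an intention-to-treat mixed model can use partial follow-up. This stands too, so 79% is a conditional illustration rather than a forecast. It does not rescue the 28% statement, which remains a relabelled dropout allowance.

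Two further criticisms should not be pressed. Power of 86.8% at ICC 0.05 is ordinary sensitivity, since the section does not claim 90% across the ICC range. And 12% can be a joint rate of failing WHOeyes and meeting the other entry criteria, so it need not contradict a 40% failure rate; the label is ambiguous and no power figure depends on it.

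**Conclusion.** The reported inputs are wrong as written. Six sequences contradict the trial's five (30 clusters and 210 participants against 25 and 175; 97.0% against 89.7% power). The CV of 3 is nearly twice the attainable maximum of 1.60, a bound that depends on the cap of 25 per cluster. The prevalence headroom does not exist: if yield really were 28% and 30% then dropped out with no usable data, power would be about 79% (75% to 81% over ICC 0.05 to 0.01).

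The power figures rest on the assumptions listed in the working. At ICC 0.02, varying the cluster autocorrelation from 0.5 to 1 moves the five-sequence result only between 89.7% and 90.2%; a t reference with 18 to 23 degrees of freedom gives 86–87%. What is established is a set of misreported figures and one false assurance, not a proven loss of power.

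**What to change.** In the Sample size section:

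1. Restate the design as five sequences of five clusters over six 12-week periods, with a mean of seven completers per cluster (175 in all).
2. Replace the CV of 3 with the attainable value actually used, justify it, and rerun the power. The documents do not show what was intended, so the sponsor must supply the number. The binomial 0.32 is only a reference point, because it assumes no between-cluster variation in prevalence or retention.
3. Delete the statement that 28% lies below the piloted prevalence, or report the power at a true 28% yield after dropout.
4. Secondary: say whether the piloted 40% is the WHOeyes failure rate or the eligible-myopia yield among those failing, and whether 12% is a joint fail-and-eligible rate.

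The cost is one corrected paragraph and one rerun of the power calculation. No change to clusters, steps, target numbers, outcome or analysis is needed.

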### Randomisation, allocation and concealment

The random selection of clusters will occur 3 weeks prior to the scheduled date for eye examinations. The identity of the selected five clusters will not be known by the investigators or anyone involved in the trial before randomisation.

The Northern Ireland Clinical Trials Unit (NICTU) will use a centralised system to manage the randomisation process in collaboration with the LV Prasad Eye Institute Clinical Trials Unit (LVPEI CTU). The NICTU will advise LVPEI CTU of the clusters selected 5 weeks before the transition date. Then, LVPEI CTU will inform the site principal investigator or an individual with delegated authority of the five clusters selected. The 125 participants in these randomly selected clusters (25 participants per cluster) will then be notified of the eye examination and reminded 14 days, 5 days and 1 day in advance.

### Reporting of adverse events

The period for reporting adverse events (AE) in the trial commences when informed consent is received from a participant and terminates when the DAS unit is removed from his/her motorcycle. AEs will be recorded and reported in compliance with Vietnamese national guidelines. Any serious adverse events (SAEs) will be promptly reported using the designated form. The LVPEI CTU will be notified of all SAEs by email within 24 h and will notify the chief investigator and sponsor of all SAEs within an additional 24 h. The LVPEI CTU will notify the Queen’s University Belfast (QUB) Research Ethics Committee of all SAEs within 7 days. The local principal investigator will provide annual progress reports to the local IRB.

### Additional data collection

The following information will be collected by questionnaire from those who fail the WHOeyes self-assessment in at least one eye: age, driving experience, primary means of transport, distance driven per week, motorcycle type, brand, model and engine capacity, and possession of a driving licence. Those meeting the inclusion criteria for DAS fitting and providing informed consent will be asked to provide the following baseline data: exposure to eyecare assessments at time of licensure, visual function (VFQ-25) [22], driver risk profile (Dula Dangerous Driving Index [DDDI]) [24] and economic data including home location (urban or rural), income and estimated monthly expenditures. At the time of the eye examination but before the participant’s cluster transitions to the intervention condition, data will be collected on visual acuity, refractive error, details of current spectacle wear, presence of ocular abnormalities and whether spectacles are required. Data will subsequently be collected on whether spectacles are provided.

Every 2 weeks, participants meeting with study staff to exchange the removable drive in their DAS units will be asked whether they have been involved in a crash in the preceding 2 weeks. Repair and insurance costs will be recorded if a crash occurs. Financial data for the cost-effectiveness calculations from a societal perspective will be captured, including cost of health care received and for crash-related repairs.

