### Outcome measures

#### Primary outcome

The primary trial outcome is the number of CNC events per 1000 km driven. Study participants will be asked to meet with research staff every 2 weeks to exchange the USB drives from their DAS units for empty drives. Potential CNC events will be extracted from the DAS recordings using mining algorithms in which kinematic data (lateral and longitudinal acceleration due to hard braking events or the vehicle having fallen on its side) will be passed through filters to discover points at which a CNC event may have occurred. Personnel trained in video reduction will then examine the video footage of the candidate CNC event to assess the content, nature and severity.

An analysis of the probability of CNC events will require the collection and analysis of data from periods (epochs) of motorcycle use free from CNC events. The number of baseline epochs collected for each motorcycle driver will be calculated as a percentage of the total number of kilometres travelled by all drivers during the course of the study. The start-point for each baseline epoch will be randomly selected from the drivers’ video data. If the motorcycle is moving more than 5 km/h, 10 s of video data will be extracted and analysed by video reduction personnel who will record roadway (road type and condition) and traffic variables; riding behaviour (overtaking, speed); riding manoeuvres (turning or going straight, etc.); presence of passengers and environmental conditions (e.g. weather conditions) for each baseline epoch interrogated. Assessors will be masked to the participant’s allocation.

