#### Secondary outcomes

Secondary outcomes include self-reported visual function (driving-adapted Visual Function Questionnare-25 [VFQ-25]) [22] administered at baseline and 1 month after receiving spectacles; self-reported crashes and injuries reported every 2 weeks by questionnaire (Crash and Injury Self-Report Questionnaire [CI SRQ]); self-reported crashes (compared with DAS-recorded crashes); and total delivery cost per CNC event avoided in the intervention condition (as an indicator of cost-effectiveness).

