### Statistical analyses

All outcomes for trial participants will be analysed in accordance with the intention-to-treat (ITT) principle. Baseline characteristics will be summarised using means and standard deviations, medians and interquartile ranges, or numbers and percentages, as appropriate. The primary outcome (number of CNC events per 1000 km driven) will be analysed using generalised linear mixed models, reporting mean differences and adjusting for cluster, secular and time effects. For example, secular trend adjustments will take into consideration national and regional driving safety campaigns and calendar time. Seasonal factors (amount of daylight, inclement weather, etc.) are likely to play a role in the number and severity of CNC events. Analysis of secondary outcomes will be done in a similar fashion. Risk differences for binary outcomes and mean differences for continuous outcomes, all adjusting for cluster, secular and time effects, will be reported.

Sensitivity analyses will be conducted to examine the intervention effects, adjusting for additional pre-specified potential confounders including age (years as a continuous variable), DDDI risk profile [24] (total score as a continuous variable) and residence (rural/urban as a binary variable).

Missing data will likely result when participants withdraw from the study or do not complete the full follow-up. Multiple imputations of missing data when assessing secondary outcomes will involve creating 20 copies of the data and imputing missing values by chained equations before averaging the datasets [26].

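### The self-reported crash question looks back a fixed 2 weeks from an attended visit, so a missed exchange leaves days unasked, and a crash can cause the missed exchange

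*Protocol article*

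**What the plan says.** Three parts of the protocol article bear on this point.

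- **When and how crashes are asked about.** Under Primary outcome, riders are "asked to meet with research staff every 2 weeks to exchange the USB drives". Under Additional data collection, the crash question is put at that same meeting, and riders "will be asked whether they have been involved in a crash in the preceding 2 weeks". Repair and insurance costs are recorded when a crash has occurred.
- **What the answers feed.** Secondary outcomes lists "self-reported crashes and injuries reported every 2 weeks by questionnaire" (the CI SRQ) and, separately, self-reported crashes compared with those recorded by the DAS. Delivery cost per event avoided is also a secondary outcome.
- **How gaps are handled.** Statistical analyses plans "Multiple imputations of missing data when assessing secondary outcomes", using chained equations and 20 copies. It names withdrawal and incomplete follow-up as the expected sources of missing data. Binary outcomes are to be reported as risk differences.

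Two other routes can bring a crash to the trial's notice. Reporting of adverse events runs from consent until the device is removed and is not tied to visits. The DAS itself flags hard braking or a toppled motorcycle for video review.

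**The concern.** The question is anchored to the date of the visit, not to the last time the rider answered it. The two coincide only when every exchange is kept. When one is missed, the next question does not reach back over the gap, and a rider who crashed early in it can truthfully answer no.

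This matters more than ordinary missed visits because a crash can injure the rider or disable the motorcycle, and either may be why the exchange was missed. The chance of being unobserved then depends on the value that would have been observed. Three things are at stake:

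- the level of self-reported crashes and injuries, and the risk difference based on it;
- the self-report versus DAS comparison, where a drive recovered later may show a crash that the questionnaire, correctly answered, does not;
- the repair and insurance costs collected alongside the crash question.

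**Working it through.** The plan gives no figure for missed visits or self-reported crash risk, so there is nothing to reproduce. The check has two parts: what the wording covers, and what outcome-dependent loss would do.

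**1. Coverage.** Inputs: exchanges every 14 days and a look-back of 14 days (Primary outcome; Additional data collection). After k consecutive missed exchanges, the interval to the next attended visit is 14(k + 1) days, of which 14 are asked about and 14k are not.

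- k = 0: 14 of 14 days covered.
- k = 1: 14 of 28 covered, half unasked.
- k = 2: 14 of 42 covered, two thirds unasked.

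Example with exchanges due on days 14 and 28: a crash on day 3 is followed by a missed visit on day 14 and attendance on day 28. The question covers days 15 to 28, so the day-3 crash is outside it.

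**2. Number of windows.** The study lasts 72 weeks with an estimated 250 riders ("Over the 72 weeks of the study, an estimated 250 students from the 25 clusters"), so 72 / 2 = 36 windows per rider and at most 36 × 250 = 9,000 rider-fortnights. The plan also expects dropout ("With a 30% dropout rate, this will result in complete datasets for 175 participants over the course of the trial"). Counting only those 175 gives 175 × 36 = 6,300. If 5% to 15% of exchanges were missed (an assumption), 450 to 1,350 of the 9,000 windows would be affected, or 315 to 945 of the 6,300. This shows scale only; it says nothing about how many contain a crash.

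**3. Effect of outcome-dependent loss (illustration; every rate is assumed).** Let p be the true crash risk per fortnight, m the background chance of a missed visit, and s the share of crashes that cause a missed visit never recovered. The chance of missing the visit after a crash is q = s + (1 − s)m. The risk among observed fortnights is

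p(1 − q) / [p(1 − q) + (1 − p)(1 − m)].

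Since 1 − q = (1 − s)(1 − m), m cancels and this becomes p(1 − s) / (1 − ps). Imputation that assumes missing at random and has no informative auxiliary data reproduces this value. For p = 0.01 and s = 0.30: 0.007 / 0.997 = 0.00702, or 70.2% of the truth. The risk-difference columns assume a true 10% relative reduction, the effect postulated for the primary outcome under Sample size.

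| s | Observed risk, p = 1% (share of truth) | Observed risk, p = 3% (share of truth) | Risk difference, share of truth (p = 1% / 3%) |
|---|---|---|---|
| 5% | 0.00950 (95.0%) | 0.02854 (95.1%) | 95.1% / 95.3% |
| 10% | 0.00901 (90.1%) | 0.02708 (90.3%) | 90.2% / 90.5% |
| 20% | 0.00802 (80.2%) | 0.02414 (80.5%) | 80.3% / 80.9% |
| 30% | 0.00702 (70.2%) | 0.02119 (70.6%) | 70.4% / 71.2% |

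The risk ratio stays at about 0.90 throughout. So loss that is equal in both conditions shrinks the risk difference, which is the planned measure for binary outcomes, and leaves the ratio almost unchanged. If spectacles alter how often a crash leads to absence, the bias could go either way.

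**The case against.** The strongest reply is that a 2-week recall asked every 2 weeks leaves no gap, and that a gap arises only if a visit is missed and nothing catches it up. The article condenses a full protocol (version 4.2) and does not reproduce the CI SRQ. Rules for missed or rescheduled visits may be there, and their absence here is no finding. A short delay also does limited harm: a visit on day 17 still reaches back to day 3.

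This stands as a limit on the claim. It does not remove the point, because the article does state a look-back, and the one it states works only with perfect attendance.

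A reader might go further and infer that badly hurt riders are never asked about their crash, that serious adverse event reporting is late or absent for them, and that the gap is filled in from riders who attended. The documents do not support these readings:

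- Adverse event reporting does not depend on visits, and nothing shows that it would fail.
- The DAS can record a crash without the rider's recall. In partial reply, its drive is collected at the same exchange, so a missed visit may delay both sources.
- The article does not say that a single missed fortnight is imputed; that would follow only from the general rule for secondary outcomes. The imputation model is not shown and may use DAS or safety data.
- Health-care costs are described in a separate sentence and are not made conditional on the 2-week question.

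**Conclusion.** The recall window is badly fixed as worded. It makes complete ascertainment of self-reported crashes depend on unbroken attendance, in a setting where the outcome can itself cause absence. The coverage arithmetic (14 of 28 days, 14 of 42) follows directly from the text.

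The likely direction is understatement of self-reported crashes and injuries, with some false disagreement against the DAS and some lost repair and insurance costs. The size is unknown. The 95% to 70% range rests on assumed shares of 5% to 30% of crashes causing an unrecovered missed visit, on equal loss in both conditions, and on imputation without informative auxiliary data.

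The primary outcome is taken from the DAS and does not use this question, so the primary conclusion is not at risk from it. The change is worth making because it is nearly free: the two wordings are equivalent when no visit is missed, and the revised one is better when a visit is.

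**What to change.** 1. Ask about crashes *since your last completed crash questionnaire*, and record the date of each crash. Dates let a crash reported late be assigned to the right fortnight and, if the gap spans the cluster's transition, to the control or intervention condition.
2. Analyse self-reported crashes over the time each questionnaire actually covers, so that a longer interval is not treated as a standard fortnight.
3. Where a fortnight remains unobserved, use serious adverse event and DAS records as auxiliary information in the imputation. Keep the self-report variable separate and unfilled for the comparison with the DAS, so that the comparison stays independent.

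The cost is one reworded item, one date field and a short addition to the analysis. The downside is a longer and unequal recall period after a missed visit, with somewhat poorer recall of minor crashes. If the full protocol or the CI SRQ already asks back to the last completed questionnaire, the wording under Additional data collection only needs to be brought into line with it.
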